### Outcome measures

At baseline, the following assessment parameters will be registered (Fig. 1): age and sex; etiology and duration of CP; past history of acute pancreatitis; current alcohol and smoking status; the presence of CP complications, including exocrine pancreatic insufficiency and diabetes mellitus; cross-sectional imaging results; current medications, including analgesics; and past history of endoscopic and surgical treatment. Data will be collected using a paper case report form and later entered into an electronic database with double data entry check.

**Fig. 1 Fig1:**
[figure not shown]
Schedule of enrollment, interventions, and assessments. ^a^Baseline variables: age; sex; etiology and duration of chronic pancreatitis (CP); history of acute pancreatitis; current alcohol and smoking status; complications of CP, including exocrine pancreatic insuficiency (EPI) and diabetes mellitus; cross-sectional imaging results; medications, including analgesics; and past history of endoscopic and/or surgical treatment. ^b^Primary outcome: Pain scores documented in a weekly pain diary based on a 0–10 visual analogue scale. ^c^Secondary outcomes: Pain scores after 6 months, > 30% pain relief, number of pain-free days, analgesic consumption, frequency of hospitalizations, quality of life (European Organization for Research and Treatment of Cancer Quality of Life questionnaire), pain and physical functioning composite scores (modified Brief Pain Inventory–short form), anxiety and depression scores, patient global impression of change, and complications. ^d^Quantitative sensory testing assessment parameters. *ERCP* Endoscopic retrograde cholangiopancreatography, *ESWL* Extracorporeal shock wave lithotripsy

The follow-up duration is 6 months from randomization with scheduled visits after 3 months (primary study period) and 6 months (follow-up). The questionnaires and pain diary used for collection of clinical endpoints are described in the previous sections on primary and secondary clinical endpoints. In addition, QST profiles will be recorded prior to intervention as well as 24–48 h after and 3 months after intervention. A schedule for the study assessment parameters is provided in Fig. 1.

### Quantitative sensory testing

#### Repetitive pinprick stimulation (temporal summation)

Recording of temporal summation to repetitive pinprick stimulations in the pancreatic and control areas (midline volar site of dominant forearm) will be employed using a 256-nm von Frey hair (Pin-Prick Stimulatoren; MRC Systems GmbH, Heidelberg, Germany). Pain ratings using a 0–10 numerical rating scale will be obtained after a single application and after the last application in a series of ten repetitive stimuli with an interstimulus interval of 1 s. For accurate timing of the stimuli, the procedure is guided by an auditory signal using a metronome. The difference between the last and the first pain ratings of the ten stimuli will be recorded as the temporal summation score.

#### Muscle pressure stimulation

The pressure pain detection threshold (PDT) and pain tolerance threshold (PTT) will be determined for the following skin dermatomes: C5 (clavicula), T10 ventral (upper epigastric area; pancreatic viscerotome), T10 back (pancreatic viscerotome), L1 (anterior superior iliac crest), and L4 (the quadriceps 15 cm above the patella). All lateralized pressure stimulations will be applied on the patient’s dominant side. An electronic pressure algometer (AlgoMed; Medoc Ltd., Ramat Yishai, Israel) with a probe surface area of 1 cm^2^ will be used for the pressure stimulations. Pressure will be increased in two separate sessions at a rate of 30 kPa/s until the PDT or PTT is reached. The assessment parameter is the pressure at the predefined sensory threshold measured in kilopascals.

#### Cold pressor test

The dominant hand is immersed in an ice-chilled water bucket (2.0 °C ± 0.3 °C). The patient will be told to remove the hand from the water after 2 min of immersion or sooner if the pain is intolerable. The patients rate the pain intensity for every 10 s during the cold pressor test using a 0–10 VAS. If the patient withdraws their hand sooner than 2 min because of intolerable pain, the VAS will be considered to be 10 for the remaining period of time, and the time for withdrawal of the hand will be noted.

#### Conditioned pain modulation

CPM is a clinically measurable form of descending pain modulation that can be induced experimentally by a conditioning stimulus (the cold pressor test) and quantified by applying a “test pain” (pressure stimulation on the nondominant quadriceps musculature 4 cm above the patella) before and after the conditioning stimulus [36]. The difference in pressure stimulus intensity (PTT) before and after the cold pressor test provides a quantitative index of the CPM capacity in the individual patient. The techniques used for pressure stimulation and cold pressor test described above will be combined to measure CPM.

### Pancreatic imaging

Cross-sectional imaging (CT and MRCP) will be used to evaluate the pancreatic morphology prior to study enrollment based on usual clinical practice. All patients enrolled in the study will have their imaging parameters reviewed and described by an expert radiologist ([name]).

### Statistical analysis

The primary analysis of clinical endpoints will be by intention to treat, meaning that all randomized patients are included in their initially assigned study arm, regardless of adherence to the study protocol. Experimental endpoints will be evaluated by per-protocol analysis, meaning that only patients completing the experimental setup will be included. A repeated measures linear mixed effects model will be used for the primary analysis and will include terms for treatment group, assessment time point (week), and the interaction of treatment with assessment time point. Summary statistics of pain scores will be provided for the individual time points, and the difference in pain scores between groups after 3 months is considered the primary efficacy parameter. Subgroup and covariate analyses will be performed if applicable and in case differences in patient subgroups deemed clinically relevant are evident. Subsequent analyses directed at the secondary, experimental, and safety endpoints are analyzed using appropriate statistics, including mixed effect models, Fisher’s exact tests, and Student’s *t* tests or Wilcoxon rank-sum tests as appropriate. The predictive value of the QST profiles will be analyzed using logistic regression models.

We plan to conduct an interim analysis after approximately one-third of patients (*n* = 40) have been randomized and have completed 6 months of follow-up, using a two-sided significance test with the O’Brien–Fleming spending function and a type I error rate of 5%. An independent statistician, blinded to the treatment allocation, will perform the interim analysis. The statistician will report to an independent data and safety monitoring board (DSMB). The DSMB will have unblinded access to all data and will decide on the continuation of the trial and report to the internal review board of the Asian Institute of Gastroenterology. If there is a highly significant difference in improvement in pain in the treatment arm, then all subsequent patients will be subjected to this. The trial will not be stopped in case of futility, unless the DSMB advises otherwise during the course of safety monitoring.

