### Outcomes

The study consists of a clinical part and an experimental part. The clinical part of the study aims to investigate the pain-relieving effects of combined ESWL and endoscopic treatment in patients with painful CP in comparison with sham treatment. The experimental part of the study aims to evaluate if QST profiles obtained prior to ESWL and endoscopic intervention can be used for prediction of treatment outcome.

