#### Experimental endpoints

The following experimental pain measures will be employed prior to intervention as well as 24–48 h and 3 months after intervention to characterize changes in pain processing induced by the assigned procedures:
Muscle pressure stimulation (pancreatic viscerotome [T10 ventral and dorsal] and control areas [C5, L1 and L4])Bone pressure stimulation (tibia bone)Temporal summation to repetitive pinprick stimulations of the pancreatic area (T10) and control area [dominant forearm])Conditioned pain modulation (CPM)

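### Limiting QST endpoints to patients who complete the experimental setup selects on a post-randomization event and, if applied to the prediction model, drops usable patients

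*Protocol article*

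**What the plan says.** The Statistical analysis section sets two analysis populations. Clinical endpoints are analysed by intention to treat, so that "all randomized patients are included in their initially assigned study arm, regardless of adherence to the study protocol". For the experimental endpoints the rule is: "Experimental endpoints will be evaluated by per-protocol analysis, meaning that only patients completing the experimental setup will be included".

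The Experimental endpoints section lists the QST measures and schedules them "prior to intervention as well as 24–48 h and 3 months after intervention to characterize changes in pain processing induced by the assigned procedures". That makes three sessions, two of them after the procedures.

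The Outcomes section gives the aim of the experimental part as evaluating whether "QST profiles obtained prior to ESWL and endoscopic intervention can be used for prediction of treatment outcome". On method, the Statistical analysis section says: "The predictive value of the QST profiles will be analyzed using logistic regression models". It names no separate analysis set for that model. It also says: "Subsequent analyses directed at the secondary, experimental, and safety endpoints are analyzed using appropriate statistics, including mixed effect models".

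**The concern.** Two different uses of QST may fall under one completer rule.

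**Change in pain processing.** The stated purpose is "to characterize changes in pain processing induced by the assigned procedures". Attributing a change to the assigned procedure requires comparing the arms. Patients who attend all later sessions are a subset formed after treatment, and within it the arms need not remain comparable. Differential completion is plausible. At the 24–48 h session one arm has had epidural anesthesia, lithotripsy (possibly repeated the next day) and sphincterotomy. The other has had a pinprick and a duodenoscopy without ductal intervention. Monitoring and safety acknowledges that ERCP raises the risk of acute pancreatitis.

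The rule also does not do the usual job of a per-protocol set. As worded, it selects on completing measurements and not on receiving the treatment as planned.

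**Prediction.** The aim in Outcomes needs the pre-intervention QST profile and the later clinical outcome. Pain comes from a diary supported by weekly telephone calls, so a patient who misses a later QST session can still have the 3-month pain score. Excluding that patient loses information. If the patients who do badly are the ones who skip sessions, it could also under-represent non-responders.

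**Working it through.** **1. The plan's own figure.** No sample size is given for QST. The figure for the primary endpoint (Sample size determination: difference 30%, SD 45%, power 90%, two-sided 0.05) reproduces:

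n per arm = 2 × (1.960 + 1.282)² × (45/30)² = 47.3, rounded up to 48.

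The total is 96, and 96 × 1.10 = 105.6, so 106. The present point does not depend on this figure; it supplies only the 106 patients and the 10% dropout used below.

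**2. When inclusion is decided.**

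| QST use | Data needed | Decided by the completer rule |
|---|---|---|
| Change between arms | Baseline plus at least one later session | After randomization and treatment |
| Prediction of 3-month pain | Baseline QST plus 3-month pain score | After randomization and treatment, if the rule applies |

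In both rows the rule can ask for more than the analysis needs.

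**3. Precision lost (assumed completion rates).** Expected dropouts are 0.10 × 106 ≈ 11, leaving 95. Suppose these 11 are among the non-completers and have no 3-month outcome. Then the recoverable patients are the non-completers minus 11, and the standard-error ratio is sqrt(95 / completers).

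| Assumed non-completion | Non-completers | Completers | Recoverable | SE ratio |
|---|---|---|---|---|
| 10% | 11 | 95 | 0 | 1.00 |
| 20% | 21 | 85 | 10 | sqrt(95/85) = 1.057 |
| 30% | 32 | 74 | 21 | sqrt(95/74) = 1.133 |

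At 20% the avoidable loss is about 6%. For QST change at 3 months this is an upper bound, because a patient who missed that session still has no 3-month QST value.

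**4. Possible bias (assumed mechanism).** Assume no true effect on QST change, 53 patients per arm, and non-completion driven by a normal variable with correlation ρ to QST change. With a fraction p not completing, the completers' mean shifts by ρ × φ(z_p)/(1 − p), in SD units. The factor φ(z_p)/(1 − p) is 0.109, 0.195, 0.350 and 0.497 for p = 5%, 10%, 20% and 30%. Bias is the difference in shift between arms. The standard error is sqrt[1/(53(1−p₁)) + 1/(53(1−p₂))]. Type I error is P(|Z + bias/SE| > 1.96).

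| Non-completion by arm | Bias, ρ = 0.3 to 0.5 | Type I error |
|---|---|---|
| 10% vs 10% | 0 | 5.0% |
| 10% vs 20% | 0.05 to 0.08 SD | 5.6% to 6.6% |
| 5% vs 20% | 0.07 to 0.12 SD | 6.4% to 8.9% |
| 10% vs 30% | 0.09 to 0.15 SD | 7.0% to 10.6% |

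Worked case, 10% vs 20% with ρ = 0.5: bias = 0.5 × (0.350 − 0.195) = 0.078; SE = sqrt(1/47.7 + 1/42.4) = 0.211; ratio 0.37; type I error 6.6%.

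Under this mechanism, bias requires completion to depend on arm and on QST change together. It vanishes when the rates are equal.

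**The case against.** The strongest reply has four parts.

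**The scope is inferred.** The article does not define the experimental setup as every session and every test. The Abstract calls QST a substudy, and the phrase could mean patients who underwent QST at all. Listing mixed models for these endpoints fits a looser reading. This stands as a limit on certainty. Still, with three scheduled sessions, all of them is the natural reading, and the ambiguity itself needs removing.

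**Prediction may not be covered.** The logistic regression has its own sentence, its predictor is baseline QST, and the responder outcome is clinical. A reader might infer that the completer rule is stated for all QST analyses. It is not: the text implies this only by placing prediction in the experimental part. The Abstract also describes prediction more loosely, from QST before and after intervention. That half of the point is therefore conditional.

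**The QST comparison is secondary.** The only QST hypothesis under Study hypothesis and aim concerns prediction, and no power is claimed for QST. This is correct and limits the consequence. The purpose stated under Experimental endpoints nevertheless attributes change to the assigned procedures.

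**Bias is not shown.** Nothing in the article shows that completion differs by arm. Early hand withdrawal in the cold pressor test is scored, in that "the VAS will be considered to be 10 for the remaining period of time", so intolerable pain there need not be missing data. Acute pancreatitis after lithotripsy is described as very infrequent. A reader might infer that the rule wrecks the randomized comparison or removes the non-responders. The documents support only that the safeguard is lost and that such selection is possible.

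**Conclusion.** The point holds in limited form. The completer rule is a stated choice and not a detail left to an analysis plan. Read with the three-session schedule, it makes inclusion depend on a post-randomization event. The comparison of QST change between arms then no longer rests on randomization alone. Whether it is actually biased, and by how much, cannot be determined from the article. Under the assumed scenarios bias runs from zero to about 0.15 SD.

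For prediction, the loss of usable patients follows only if the same rule is applied there. At an assumed 20% non-completion that includes the planned dropouts, about 10 patients are recoverable and standard errors are about 6% larger than necessary.

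A figure of 12%, from 1/sqrt(0.8), might suggest itself. It compares completers with 106 fully observed patients, which no analysis can deliver once dropout has occurred.

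The primary endpoint is analysed by intention to treat and is untouched. The change is worth making before analysis, for the mechanistic and predictive results.

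**What to change.** Replace the completer sentence in the Statistical analysis section with three statements:

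- QST change is analysed in all randomized patients with baseline QST, in their assigned arm, with a mixed model that uses every available session.
- The prediction model includes every patient with baseline QST and the 3-month pain outcome.
- The completers-only analysis is kept as a sensitivity analysis, with completion of the experimental setup defined by session and test.

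It would also help to report QST completion by arm and session, so that readers can judge how far selection matters.

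The mixed model is not a complete remedy. It relies on missing sessions being explained by the observed data, and it cannot supply a 3-month QST value that was never measured. It does use the partial data that the present rule discards.

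The cost is a few sentences of text. Mixed models are already listed for these endpoints, and no new data, visits or patients are needed.

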### Monitoring and safety

Prior to trial initiation, a DSMB comprising a neurologist, an anesthesiologist, and a statistician (all from outside the study center) will be constituted. The DSMB will conduct periodic monitoring to ensure that the protocol and good clinical practice standards are followed. The monitors may review source documents to confirm that data recorded on case report forms are accurate. The investigator and institution will allow the DSMB and appropriate regulatory authorities direct access to source documents to perform this verification. The trial site may be subject to review by the institutional review boards, and/or to quality assurance audits performed by the DSMB, and/or to inspection by appropriate regulatory authorities. The DSMB will also conclude on the planned interim analysis.

There is no anticipated harm or compensation for trial participation. The ESWL and ERCP procedures on patients with CP are currently used in daily clinical practice, and participation in the study is not expected to be associated with an increased risk of adverse events compared with standard clinical care. Following ESWL, we have observed mild erythema at the site of stimulation. There has been a very infrequent incidence of acute pancreatitis after the procedure. Because ERCP is associated with an increased risk of post-procedure acute pancreatitis, means to decrease this risk (rectal indomethacin and preprocedural intravenous fluids) will be used in high-risk patients.

## Discussion

Pain is the primary symptom of CP and is associated with poor health-related outcomes, including reduced life quality, disability, and increased health resource use [37–39]. Pain treatment is unsatisfactory in a large proportion of patients and generally based on low-quality evidence in particular for invasive treatments (endoscopy and surgery) [14]. The SCHOKE (Extracorporeal Shock Wave Lithotripsy and Endotherapy for Pain in Chronic Pancreatitis) trial is a randomized, sham-controlled trial designed to determine if pancreatic duct decompression is an effective approach for obtaining pain relief in patients with CP. According to current guidelines, invasive procedures are recommended for pain treatment in the context of CP, and some practitioners even advocate for surgical treatment in the early phase of CP [32, 40, 41]. However, neither surgery nor endoscopic therapy has been thoroughly evaluated in sham-controlled trials [14]. The present study will, for the first time, provide sham-controlled evidence for the effectiveness of pancreatic duct decompression as a remedy to relieve pain in CP.

The mechanisms responsible for pain in patients with CP are multifactorial, and thus it is to be expected that no treatment can effectively relieve pain in all patients [42]. Identification of biomarkers that link pain mechanisms with specific treatment modalities is therefore an unmet need in the field, but there are currently few personalized approaches to pain treatment in CP [29]. For example, the presence, severity, and temporal nature of pain correlate poorly with imaging findings, and, as such, imaging can only be used to identify cases in which an invasive treatment is technically feasible, but it cannot be used to determine if patients will benefit from the planned treatment [7, 8, 43]. A QST protocol designed for characterization of pancreatic pain has previously shown effectiveness for the prediction of analgesic outcome in patients with CP and may serve as a useful biomarker for endoscopic treatment efficacy as well [24]. The SCHOKE trial therefore includes a QST testing paradigm specifically developed to assess and characterize pain in CP [29].

In conclusion, the SCHOKE trial is a randomized, sham-controlled trial that investigates whether pancreatic duct decompression is effective for obtaining pain relief in patients with painful CP.

## Trial status

Ethical approval has been obtained, and the trial was registered with ClinicalTrials.gov on May 25, 2019 (NCT03966781). The first patient was randomized by January 4, 2020, and recruitment is expected to be completed July 1, 2021.

## Data Availability

Patients are coded using a numeric randomization code (anonymized), and only the principal investigators have access to this code. The source data are kept by the project leader for 15 years at the data center of the Asian Institute of Gastroenterology. All data generated or analyzed during this study will be included in the published results. Any data required to support the protocol can be supplied on request. The datasets analyzed during the current study are available from the corresponding author on reasonable request.

## Abbreviations

CP: Chronic pancreatitis
CPM: Conditioned pain modulation
CT: Computed tomography
DSMB: Data and safety monitoring board
ERCP: Endoscopic retrograde cholangiopancreatography
ESWL: Extracorporeal shock wave lithotripsy
MRCP: Magnetic resonance cholangiopancreatography
PDT: Pain detection threshold
PTT: Pain tolerance threshold
QST: Quantitative sensory testing
RCT: Randomized controlled trial
SCHOKE: Extracorporeal Shock Wave Lithotripsy and Endotherapy for Pain in Chronic Pancreatitis
SPIRIT: Standard Protocol Items: Recommendations for Interventional Trials
VAS: Visual analogue scale
